## Abstract

Valproate is the most effective treatment for idiopathic generalised epilepsy. Currently, its use is restricted in women of childbearing potential owing to high teratogenicity. Recent evidence extended this risk to men’s offspring, prompting recommendations to restrict use in everybody aged <55 years. This study will evaluate mortality and morbidity risks associated with valproate withdrawal by emulating a hypothetical randomised-controlled trial (called a “target trial”) using retrospective observational data. The data will be drawn from ~250m mainly US patients in the TriNetX repository and ~60m UK patients in Clinical Practice Research Datalink (CPRD). These will be scanned for individuals aged 16–54 years with epilepsy and on valproate who either continued, switched to lamotrigine or levetiracetam, or discontinued valproate between 2014–2024, creating four groups. Randomisation to these groups will be emulated by baseline confounder adjustment using g-methods. Mortality and morbidity outcomes will be assessed and compared between groups over 1–10 years, employing time-to-first-event and recurrent events analyses. A causal prediction model will be developed from these data to aid in predicting the safest alternative antiseizure medications. Together, these findings will optimise informed decision-making about valproate withdrawal and alternative treatment selection, providing immediate and vital information for patients, clinicians and regulators.

## Introduction

Epilepsy impacts 70 million people worldwide [1]. Valproate is one of the most effective drugs for treating epilepsy, outperforming any other in idiopathic generalised epilepsy, which affects a third of people with epilepsy (PWE) [2,3]. It was the most prescribed antiseizure medication (ASM) globally in the early 2000s [4]. However, widespread evidence demonstrating foetal congenital malformations (11%) and neurodevelopmental disorders (30–40%) associated with prenatal valproate exposure led to guidance changes between 2015–2018 [5]. These prohibited valproate prescribing in women of childbearing potential unless other ASMs had failed, subsequently halving prescriptions in women [4,5].

Valproate remains the first-line ASM for men with newly diagnosed generalised epilepsy in most countries [2,3]. In the UK, regulators recently considered valproate’s known risks of impaired male fertility, emerging pre-clinical evidence of transgenerational risks with prenatal exposure, and animal studies suggesting adverse effects on testes [5,6]. In response, they announced a phased implementation (from January 2024) of recommendations restricting valproate prescribing for both men and women aged <55 years unless other ASMs have failed [5,6]. Similar restrictions are being considered in other countries [7–9]. Together, they are likely to result in withdrawal of valproate from a substantial number of men already taking it, as has been the case for women [4,5].

To support informed and safe decision-making [10], it is vital to provide these young men and women and their clinicians with comprehensive information on the safety of valproate withdrawal. Whether there are any potential risks of personal harm or morbidity (including hospital admissions, injuries, or death) associated with valproate withdrawal has not yet been quantified for either men or women on valproate [10–17]. Existing studies have focused on the group of PWE in remission from seizures for ≥2 years, usually showing seizure relapse in generalised epilepsy. They have tended to be single-centre or small, looking at seizures alone or assessing women alone [11–17]. A valproate decision support tool is available from NHS England for patients and clinicians (www.t.ly/NFi5m), designed by our centre [10]. Figures for the risks of teratogenicity on valproate are provided on page 4 of the tool as 8–37 per 100 babies [10]. However, on the same page, the “risks to you” section from withdrawing from valproate and switching to another ASM remains devoid of any figures [10], illustrating the insufficiency of current evidence to address this question.

The rise of digital care records has transformed treatment evidence generation by enabling both immediate and extensive analysis of national and international cohorts [18]. This approach overcomes limitations in sample size, cost, and time associated with completing prospective studies while also facilitating exploration of previously unexamined patient outcomes. TriNetX [19], the world’s largest real-world electronic health data platform, harbours 70 billion date- and patient-indexed electronic clinical observations from ~250m patients across 19 countries, predominantly in America but also Europe, Middle East, Africa, and Asia [18,19].

We recently published a study of 8,991 men and 5,243 women aged 16–54 with epilepsy taking valproate in TriNetX [20]. This was a survival analysis assessing 5-year mortality and morbidity in those withdrawn from valproate between 01/06/2015–01/06/2018 (regardless of whether switched to another ASM), with propensity-matched comparisons to those who remained on valproate. Results suggested substantially increased risks of emergency department (ED) attendances, hospital admissions, falls, injuries, burns and new-onset depression in both men and women withdrawn from valproate [20]. However, these were aggregate data designed to scope potential trends and generate hypotheses, not to probe causal links.

To progress the field, we propose a comprehensive study examining mortality and morbidity outcomes in individuals who either continued valproate, switched to lamotrigine or levetiracetam, or discontinued valproate. Employing a novel approach known as target trial emulation [21,22], this study will replicate a hypothetical randomised-controlled trial (RCT) using person-level retrospective observational data from both TriNetX and Clinical Practice Research Datalink (CPRD, which encompasses 60m UK patients) [23]. Target trial emulation minimises confounder and selection biases in observational studies by statistically emulating randomisation at baseline (time 0) [21]. Individuals are then analysed based on the treatment strategy aligned with their data. Results are available quickly and shown to mirror those of an RCT [21]. This offers a cost-effective and immediate alternative to conducting an RCT [21]; crucial given the urgency for information on valproate withdrawal safety amidst ongoing regulatory changes [24,25]. Additionally, the emulation facilitates creation of causal prediction models [26]. These are developed using observed data alongside causal theory and assumptions to calculate predicted risk under different hypothetical treatment conditions, allowing “what if” questions to be addressed for each potential (counterfactual) outcome [26]. This facilitates actionable prevention [26].

### Aims

Identify whether there are any differences in mortality or morbidity outcomes between remaining on valproate compared with valproate withdrawal and switch to lamotrigine, levetiracetam, or no new ASM.Develop and validate a causal prediction model that clinicians and patients could use when planning to withdraw from valproate to predict which of these alternative ASMs would have the lowest mortality and morbidity, taking baseline clinical and demographic characteristics into account.

### Hypotheses

Some morbidity or mortality outcomes will be increased when valproate is withdrawn, regardless of whether switched to lamotrigine, levetiracetam, or no new ASM;The causal prediction model developed will be able to predict which alternative ASMs are safest.

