*Causal estimand*: Assesses impact of treatment arms 1–3 vs. 4 on outcome (per-protocol assumption as observational data limits ITT assessment) [21].

*Start and end of follow-up*. The start of follow-up (Time 0 or index date) will be defined as when valproate treatment discontinued (treatment arms 1–3) or prescription of valproate at a matched time (arm 4). For time-to-first-event analyses, the end of follow-up will be defined as when the outcome occurs, censoring (including deviation from assigned treatment or leaving the study catchment area), or 10 years. For recurrent events analyses, alongside censoring as above, the end of follow-up will be 10 years, allowing for all events to be assessed throughout follow-up.

*Statistical analysis*: mirrors target trial section.

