### Sample size calculation

See Table 1.

**Table 1 pone.0306226.t001:** Sample size calculation.

Outcome: Emergency department attendance (a global measure of morbidity and a good predictor of mortality) Data source: Mbizvo *et al*. [20]			
**Target trial emulation phase**		**Prediction model phase**	
**Method**	# Proportions from the pilot study p1 <- 2977 / 8021 # valproate withdrawn group p2 <- 2471 / 8021 # group remaining on valproate # Set significance level and power alpha <- 0.05 power <- 0.80 # Z-values for two-tailed test z_alpha <- qnorm(1—alpha / 2) z_power <- qnorm(power) # Calculate sample size n <- ceiling((z_alpha + z_power)^2 * ((p1 * (1—p1)) + (p2 * (1—p2))) / (p1—p2)^2) # Display the result cat("Sample size needed for the target trial emulation study:", n, "\n")	**Method**	Sample size criteria from our previous work for developing a time-to-event prediction model to estimate the minimum required sample size for our model development are used [33].
**Result**	The minimum sample size in the target trial emulation study is 881.	**Assumptions**	
		**(i)**	We target an overall shrinkage factor of 0.9.
		**(ii)**	We assume the outcome rate to be 0.068, calculated using the 5,448 events that occurred out of 16,042 patients within the pilot study, with a median survival time of 5 years.
		**(iii)**	The performance of the model would achieve 15% of the maximum possible cox-snell R-squared for the given outcome rate.
		**(iv)**	We would consider 20 candidate predictor parameters within the model development process.

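### Table 1's minimum of 881 is a per-group size for one pooled contrast; in four equal arms it gives about 61%, not 80%, power to show harm in all three withdrawal arms on one outcome

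*Protocol article*

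**What the plan says.** The Hypotheses section states: "Some morbidity or mortality outcomes will be increased when valproate is withdrawn, regardless of whether switched to lamotrigine, levetiracetam, or no new ASM". The eligibility and treatment-arm text defines three separate withdrawal arms (switch to lamotrigine, switch to levetiracetam, no new drug) and a fourth arm that continues valproate. The causal estimand is given as "Assesses impact of treatment arms 1–3 vs. 4 on outcome", without saying whether arms 1–3 are pooled or each compared with arm 4.

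Table 1 sizes this phase on emergency department attendance. Its inputs are two proportions, "p1 <- 2977 / 8021 # valproate withdrawn group" and "p2 <- 2471 / 8021 # group remaining on valproate", with "alpha <- 0.05 power <- 0.80" and "Z-values for two-tailed test". The formula is the unpooled comparison of two proportions: "n <- ceiling((z_alpha + z_power)^2 * ((p1 * (1—p1)) + (p2 * (1—p2))) / (p1—p2)^2". The result is worded as a figure for the whole study: "The minimum sample size in the target trial emulation study is 881". According to the Introduction, the withdrawn group in the pilot was taken without regard to any replacement drug.

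The feasibility row compares this minimum with about 14,234 TriNetX patients, around a third of them withdrawn, and judges that sufficient. It also cites a CPRD search that found 29,332 men and 15,315 women. It gives no expected number for any single withdrawal arm.

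**The concern.** Two things do not match. First, a per-group number for a two-group comparison is presented as the minimum for a study with four groups. Second, the comparison that was sized (everyone withdrawn against everyone continuing) is not the one that the hypothesis and the arm structure point to. Showing harm under each of three strategies requires three contrasts to succeed together, and the probability of that is below the 80% attached to one.

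The Pathways to impact section intends the Aim 1 figures for the patient-facing section on the risks of changing medication in a national decision tool. If a pooled result, or harm seen mainly in one arm, were presented as harm whatever the replacement, patients considering a particular switch would be misinformed. Conversely, if the smallest arm were close to the stated minimum or below it, a real common harm could fail to show there and be taken as evidence that this switch is safe. Calling the sample sufficient because it exceeds 881 does not test either possibility.

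**Working it through.** **Inputs from Table 1.** p1 = 2977/8021 = 0.3712 (withdrawn); p2 = 2471/8021 = 0.3081 (continuing); difference d = 0.0631; two-sided alpha 0.05; power 0.80.

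**Step 1: reproduce 881.**
n = (1.960 + 0.842)² × [p1(1−p1) + p2(1−p2)] / d²
= 7.849 × (0.2334 + 0.2132) / 0.003980 = 880.7, rounded up to 881.
The figure reproduces. In this formula n is the size of each of the two groups, so the single contrast needs 2 × 881 = 1,762 patients.

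**Step 2: three contrasts sharing arm 4.** Assumptions not in the documents: four equal arms, the same pilot effect in each withdrawal arm, and unweighted comparisons of proportions.
- Each contrast: standard error √[(0.2334 + 0.2132)/881] = 0.0225; expected z = 0.0631/0.0225 = 2.80; power = Φ(2.80 − 1.96) = 80.0%.
- Correlation between contrasts from the shared arm: 0.2132/(0.2334 + 0.2132) = 0.477.
- Probability that all three exceed 1.96 (trivariate normal): 60.7%. A binomial simulation with 400,000 runs gives 61.2%. If the contrasts were independent it would be 0.80³ = 51.2%.

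**Step 3: size for 80% joint power.** With the same assumptions, 1,230 per arm give 91% per contrast and 80% jointly.

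**Step 4: literal reading of 881.** If 881 were the total, 881/4 ≈ 220 per arm. Each contrast then has about 29% power, and all three about 9%.

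**Step 5: what the cited TriNetX numbers would give.** 14,234/3 ≈ 4,745 withdrawn and 14,234 − 4,745 = 9,489 continuing. The split over arms 1–3 is not given, so a range is shown, listed from the smallest arm. It assumes that everyone withdrawn falls in one of the three arms and ignores losses from weighting and censoring.

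| Split of 4,745 | Smallest arm | Power in smallest arm | Joint power |
|---|---|---|---|
| equal thirds | 1,582 | 99.8% | 99% |
| 20/40/40 | 949 | 97% | 97% |
| 10/30/60 | 474 | 79% | 79% |
| 5/35/60 | 237 | 51% | 51% |

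In the last three rows joint power almost equals power in the smallest arm. With so large a continuing arm, the smallest withdrawal arm decides the matter.

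**Step 6: sensitivity to lost information.** If weighting, censoring at deviation from the assigned strategy, and switches to drugs outside arms 1–3 halved the effective numbers in every arm (an assumption), joint power would be 81% with equal thirds, 72% at 20/40/40 and 46% at 10/30/60.

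**The case against.** The strongest reply is that 881 is a floor in a study that takes every eligible patient from very large databases, so 61% describes a study that nobody intends to run. This largely stands. Even with only 881 in each withdrawal arm, a continuing arm of 9,489 would raise joint power to 89%. A reader might infer that the study is underpowered for its hypothesis. The documents do not support that: no arm sizes are given, and plausible splits run from ample to inadequate.

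A reader might also take 61% as the power of Hypothesis 1. It is not. The hypothesis speaks of some outcomes among a long list, and the calculation concerns one outcome with a common effect in every arm.

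Third, the hypothesis could mean the pooled withdrawn group, since the Introduction uses similar wording for the pooled pilot. That reading is possible. But this protocol defines the three arms separately, Aim 1 names each replacement, and Aim 2 exists to tell the alternatives apart, so three contrasts is the more natural reading. The wording should settle which is meant.

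Finally, a decision rule may sit in an analysis plan that is not shown, so its absence here is not counted as a fault. Nor is there a problem of false positives across arms: if all three contrasts must succeed, each can be tested at 5% without adjustment. What remains is a stated figure that is mislabelled and sized for a different comparison.

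**Conclusion.** The point holds in a limited form. Table 1 presents as the study minimum a number that its own formula yields per group for one pooled contrast. Taken as 881 per arm, it delivers the stated 80% power for each contrast but about 61% for all three on emergency department attendance; taken literally as a total, about 9%. These figures rest on equal arms, the pooled pilot effect in every withdrawal arm, and no loss of precision from weighting or censoring. Effects that differ between arms would change them.

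The shortfall is in the stated minimum and in the way feasibility is judged against it. It is not shown to be in the study itself, which could have about 99% joint power or about 51%, depending on how the withdrawn TriNetX patients divide. Exceeding 881 is therefore not enough to call the sample sufficient for a claim about all three strategies.

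**What to change.** 1. In Table 1, label 881 as the number per arm for one contrast with arm 4, and say that the effect comes from a pilot pooled over replacement.
2. Add that a claim covering all three strategies on one outcome needs about 1,230 per arm for 80% power, given equal arms and the pilot effect in each.
3. Judge feasibility on the expected number in the smallest withdrawal arm, in TriNetX and in CPRD, with an allowance for weighting and censoring.
4. State that harm whatever the replacement will be claimed for an outcome only if each of the three contrasts with arm 4 shows an increase at two-sided 5%; no alpha adjustment across arms is needed for this rule. Otherwise, name the arms in which harm was found. If the hypothesis is meant for the pooled withdrawn group, say so and word the conclusion to match.

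The cost is a few sentences, one restated figure and counts per arm from databases already searched. The downside is a stricter claim and a less favourable stated figure.

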### Benefits to PWE

This study will benefit PWE as substantial numbers of young men and women may soon be invited by their clinicians to come off valproate owing to both current and new regulatory changes [5,6]. Whilst this is justified in terms of preventing teratogenic harm, the patients will wish to know what the risks of withdrawing from valproate are for their own health [24,25]. This study will provide immediate evidence to help doctors answer that question [10]. It will also help patients make safer decisions over switching to alternative ASMs by generating the first ever causal prediction tool for this purpose [26]. This will be the largest study of valproate withdrawal to date, the first to assess risks in men and first to assess multiple outcomes beyond seizures alone for both men and women [11–17]. These outcomes will be collaboratively chosen with PWE through public engagement strategies, ensuring their relevance and impact on those most affected. Finally, mortality prediction is highlighted as a key recommendation for epilepsy research by NICE [27], meaning the causal prediction model generated by this study also addresses an established research need for PWE.

## Methods

### Public involvement

This study protocol (including outcome selection) was co-developed with a members of the public with lived experience of epilepsy, caring for a person with epilepsy, or taking valproate.

### Addressing Aim 1: Target trial emulation

#### Target trial design

A hypothetical target trial will be emulated in which young men and women taking valproate would be randomised to either continue valproate, switch to lamotrigine or levetiracetam, or discontinue valproate [21]. The following mortality and morbidity outcomes would be assessed over the subsequent five years:

Deaths (all-cause/epilepsy-related);ED/hospital admissions (all-cause/epilepsy-related);Seizures (symptom codes);Falls;Injuries;Burns;Aspiration pneumonia;Manic/bipolar episodes;New-onset depression;Self-harm/suicide;A composite morbidity index incorporating seizures, injuries, admissions, depression.

Intention-to-treat (ITT) and per-protocol effects would be assessed between groups [21]. Analysis would take a time-to-first-event approach (Cox-proportional hazards model) for deaths, new-onset depression and composite morbidity. A recurrent events approach (e.g., Prentice-Williams-Peterson Total Time Model) would be taken for the remaining outcomes.

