#### Target trial emulation using observational data from TriNetX and CPRD

*Eligibility criteria*. Anonymised, person-level, electronic health data will be extracted from TriNetX and CPRD, linked across primary care, ED, inpatients, outpatients, and mortality subsets. The study period will be from 01/01/2014 to 01/01/2024. Included will be men and women aged 16–54 years. The study will take an open cohort design with patients entering the cohort when the following criteria are met:

Either: ≥1 epilepsy disease or symptom code recorded during the study period and two separate valproate prescription instances over the preceding 12 months before at least one of the epilepsy disease or symptom codes;

Or: ≥1 epilepsy disease or symptom code recorded any time before the study period with at least two separate valproate prescription instances over 12 months during the study period.

TriNetX and CPRD use ICD-10-CM and SNOMED codes, respectively. The coding strategy combining disease and symptom codes with valproate, as used our published study successfully [20], was shown to accurately identify epilepsy cases in our prior work [28,29].

Treatment arms:

Withdrawn valproate and commenced lamotrigineWithdrawn valproate and commenced levetiracetamWithdrawn valproate and no new ASM commencedContinues valproate

*Treatment assignment*. Baseline (time 0) will be defined as when valproate dose reduction commences (treatment arms 1–3) or prescription of valproate at a matched time (arm 4). Eligible individuals are assigned at baseline to the treatment strategy that their data are consistent with [21]. To emulate randomisation, adjustment is made for baseline confounders using Robins’ generalised methods (g-methods, e.g., inverse probability weighting) [21], considering age, sex, ethnicity, deprivation, type of epilepsy (using G40 codes), baseline seizure frequency (symptom codes recorded over preceding 12 months), alcohol excess, developmental delay, Cambridge Multimorbidity Score, length of valproate treatment, valproate dose, and ASMs used other than valproate. The final set of covariates required to adjust for confounding will be chosen using a causal directed acyclic graph [21].

*Outcomes*. These are listed in the target trial design section and derived from our prior work [1,20,30,31], and public consultation. All coded events will be recorded for flexible categorical or continuous analyses, as needed.

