### Addressing Aim 2: Causal prediction modelling

A causal prediction model will be created using Cox-proportional hazards of time-to-first-event in a causal framework [26]. The predicted outcome will be a composite personal harms risk combining epilepsy-related deaths, seizures, injuries, admissions, and depression. Predictors for definite inclusion in the final model will be treatment arms 1–4. Candidate predictors considered in addition will be taken from the list of baseline confounders adjusted in the target trial emulation, alongside any additional variables considered to influence outcome but not treatment assignment. *A priori* clinical expertise and data-driven variable selection will refine the predictor variable list for modelling [30]. Penalisation methods (e.g., *lasso*), will be used to combine variable selection with shrinkage (reducing overfitting risks).

The model will be developed in TriNetX to help ensure it is internationally generalisable [32]. External validation will be undertaken in CPRD, facilitating subsequent clinical implementation [32]. Internal validation within TriNetX will involve 1,000 bootstrap analysis samples. Nagelkerke’s R^2^ and Brier Scores will estimate overall model performance. Calibration will be estimated with calibration-in-the-large, calibration slope, and flexible calibration plots, and discrimination with C-index. Calibration and discrimination will be reassessed within CRPD to externally validate model performance [32]. Counterfactual prediction will be embedded into the model development [26], allowing patients and clinicians to answer clinically meaningful questions such as “at the point of proposed valproate withdrawal, accounting for baseline characteristics, what is the risk of epilepsy-related death or composite morbidity for levetiracetam? And what is it for lamotrigine?”

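### As defined, the all-cause admissions outcome and both composites would count a normal delivery as morbidity, probably more often in the withdrawal arms; obstetric stays should be excluded

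*Protocol article*

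**What the plan says.** Under Target trial design, the article introduces its outcome list with "The following mortality and morbidity outcomes would be assessed over the subsequent five years". The list includes "ED/hospital admissions (all-cause/epilepsy-related", so there is an all-cause and an epilepsy-related version. It also includes "A composite morbidity index incorporating seizures, injuries, admissions, depression".

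Under Addressing Aim 2, the prediction model's outcome is "a composite personal harms risk combining epilepsy-related deaths, seizures, injuries, admissions, and depression". Deaths are limited to epilepsy-related ones there; admissions are not limited.

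The population is stated as "Included will be men and women aged 16–54 years". The Introduction says of the 2015-2018 guidance changes: "These prohibited valproate prescribing in women of childbearing potential unless other ASMs had failed".

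The baseline covariates under Treatment assignment include age, sex, developmental delay, multimorbidity and treatment history. Pregnancy and pregnancy planning are not listed, although the final set is left to a causal diagram. Under Start and end of follow-up, deviation from the assigned treatment is a censoring event. No section mentions obstetric admissions.

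**The concern.** A delivery stay is a hospital admission from some cause, so an all-cause outcome includes it. A woman who leaves valproate and later has an uncomplicated birth would have a morbidity event in the admissions outcome and, unless an earlier component event came first, in each composite.

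If births were equally common and equally observed in all arms, this would mostly add noise. There are two reasons, both arising from the protocol's own design, to expect otherwise:

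- **Common cause.** Valproate is restricted in women because of childbearing, so planning a pregnancy is a plausible reason both for withdrawal and for a later birth. It is not a listed covariate.
- **Unequal observation.** A woman in the continuing arm who stops valproate because she plans or discovers a pregnancy deviates from her assigned treatment and is censored before delivery. A woman in arms 1-3 is not censored for becoming pregnant, so her delivery is counted.

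Both push the result for women towards the first hypothesis, that some outcomes worsen on withdrawal. Under Pathways to impact, the Aim 1 figures are intended for the personal-risk section of a national decision tool, with a link to the Aim 2 model. Women considering pregnancy are among its main readers.

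**Working it through.** **The plan's own figure.** Table 1 sizes the emulation on ED attendance, with p1 = 2977/8021 = 0.3712 (withdrawn) and p2 = 2471/8021 = 0.3081 (remaining). The difference is 6.3 points. Its formula gives (1.960 + 0.842)² × [p1(1−p1) + p2(1−p2)] / (p1−p2)² = 880.7, rounded up to 881, as stated. That figure is not in dispute, and the change proposed here does not alter it.

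**Share of women.** TriNetX pilot (Introduction): 5,243 / (8,991 + 5,243) = 36.8%. CPRD feasibility search (Table 1): 15,315 / (29,332 + 15,315) = 34.3%.

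**Size of the artefact.** The documents give no birth or obstetric admission rate, so the inputs below are assumptions:

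- withdrawal has no true effect on other admissions;
- the background 5-year risk of any admission is 0.3081 in both arms (the pilot ED risk as a stand-in);
- withdrawn women have an excess 5-year probability d of an obstetric admission, independent of other admissions.

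A delivery changes the any-admission risk only in women who had no other admission. So:

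- spurious risk difference in women = (1 − p2) × d;
- pooled difference = share of women × (1 − p2) × d;
- spurious hazard ratio = ln(1 − inflated risk) / ln(1 − p2).

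Example, d = 0.05: inflated risk in women = 0.3081 + 0.6919 × 0.05 = 0.3427. The difference is 3.46 points and the hazard ratio is ln(0.6573)/ln(0.6919) = 1.14. Pooled: 0.368 × 3.46 = 1.27 points.

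| Assumed excess d (points) | Women: difference (points) | Women: hazard ratio | Pooled, 36.8% women (points) | Pooled hazard ratio | Pooled, 34.3% women (points) |
|---|---|---|---|---|---|
| 1 | 0.69 | 1.03 | 0.25 | 1.01 | 0.24 |
| 3 | 2.08 | 1.08 | 0.76 | 1.03 | 0.71 |
| 5 | 3.46 | 1.14 | 1.27 | 1.05 | 1.19 |
| 10 | 6.92 | 1.29 | 2.55 | 1.10 | 2.37 |

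**Composites.** These also count seizures, injuries and depression, so their background risk is higher and the factor (1 − background risk) is smaller. At an assumed background of 50%, the four differences in women would be 0.5, 1.5, 2.5 and 5.0 points.

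**Recurrent-events analysis.** Admissions are to be analysed as recurrent events. There the overlap discount does not apply: each extra delivery adds one event, so d points mean d more events per 100 women. The relative effect depends on the mean number of admissions per woman, which the documents do not give. The direction is the same.

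**The case against.** The strongest reply is that this is a condensed article. It gives outcome headings, not code lists, and promises to publish its coding algorithms. Obstetric stays might be dropped there, so it is not certain that births will be scored. That much stands. But a list that faithfully implements an all-cause definition includes deliveries, so the stated definition is what needs changing.

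Second, an epilepsy-related admissions outcome is already planned and largely escapes the problem. This is correct and limits the reach of the point. Neither composite says that it uses that version.

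Third, the final covariates come from a causal diagram, which may add pregnancy planning. Adjustment could then reduce the common-cause part, so it would be wrong to say that baseline adjustment cannot help. It would not by itself address pregnancies that arise later, or the censoring asymmetry.

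Fourth, the Introduction's stated exception for staying on valproate is failure of other drugs, not absence of pregnancy plans. More conceptions in arms 1-3 are therefore plausible but assumed.

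A reader might also infer two stronger things. One is that withdrawal itself causes more births. The documents do not say so, and planned pregnancy leading to both is the more direct route. If births were purely a consequence of withdrawal, all-cause admissions would still be a valid total effect, and the fault would lie in calling them harm. The other is that planned non-obstetric admissions rise after withdrawal. Nothing in the documents supports that.

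**Conclusion.** The point holds as a definitional fault that should be corrected. As written, childbirth counts as morbidity in the all-cause admissions outcome and in the unqualified admissions component of both composites, and an imbalance against withdrawal among women is credible. It rests on two assumptions: that pregnancy planning influences who is withdrawn, and that women who stop valproate for pregnancy in the continuing arm are censored as the text says.

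The size is not known from the documents. Over the assumed 1 to 10 point range, it runs from negligible (hazard ratio 1.03 in women, 1.01 pooled) to material (1.29 and 1.10). Only at the top of the range does the artefact in women reach the 6.3-point pilot difference, and that benchmark is ED attendance, not admission. A reader might infer that the study's main conclusions are invalid. The documents do not support this: the effect is confined to women, it is diluted in pooled estimates, and the other listed outcomes, including epilepsy-related admissions, are not or hardly affected.

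**What to change.** In the all-cause admissions outcome and in both composites, exclude admissions whose primary reason is pregnancy, delivery or the puerperium, unless a listed epilepsy, injury or psychiatric code is the reason for admission. For the composites, an alternative is to use the epilepsy-related admissions version and say so. Keep unrestricted all-cause admissions as a secondary description. Include pregnancy or pregnancy planning in the causal diagram, and report the admissions and composite results by sex.

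The cost is somewhat fewer events, hence slightly wider intervals, and reliance on coded reasons for admission in two code systems (ICD-10-CM in TriNetX, SNOMED in CPRD). Under Study status and timeline, data access was still being sought, so the definition can be changed before any data are seen. The sample size of 881 stays as it is.
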